## Methods

### Design and setting

This study is a comparative effectiveness experiment of a group-based walking program, Step It Up!, versus a combined program of both Step It Up! (SIU) and a civic engagement program aimed at walkability, the Change Club. We also will conduct a mixed-method implementation evaluation. At the organizational level (library), a prospective convergent parallel mixed methods design [46] will be used, in which quantitative and qualitative data will be collected in parallel, analyzed separately, and merged in order to gain a full understanding of factors that influence implementation and sustainability of the program in the libraries. At the participant level, a positive deviance approach will be used to understand experiences of high and low changers on outcomes. A sequential mixed methods design [46] will be used, with quantitative participant outcomes informing selection of participants for qualitative work.

This study will take place in 20 rural communities in Oregon. The US Institute of Museum & Library Services (IMLS) classifies libraries as serving urban, suburban, town, or rural areas using the National Center for Education Statistics (NCES) definitions for each classification [47]. The library’s classification is based on the geocoded latitude and longitude of the library’s address. For this study, libraries serving towns and rural areas are eligible. The NCES, drawing upon the U.S. Census, defines towns as areas outside of urbanized areas, but inside towns with populations between 2,500 and 50,000. This grouping of rural and town libraries follows the standard practices of libraries, as seen in organizations like the Association for Rural & Small Libraries.

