The rural communities in which the libraries are located will be matched on population, median household income, percent of residents who identify as white, walk score, rate of violent crime, percent of population 65 years or older, employment rate, percent residents without health insurance, and area deprivation index. Matched pairs will then be randomized to either a group-based walking program, Step It Up! (SIU) or the combined program (Combined) that includes both SIU and a civic engagement program, Change Club. Cluster (pairs) randomization will be implemented using the Goldilocks approach [48]. This approach involves iteratively choosing pairs that minimize distance with respect to potential confounding variables, visually assessing differences across possible randomizations, and reweighting variables by selecting confounder weights. The best pair matching was achieved by unit weighting (given weight = 1) all confounders except for population (weight = 3), walk score (weight = 3), area deprivation index (weight = 3), and percent white only (weight = 2). Libraries will be randomized prior to the start of the capacity building and training so that librarians in the SIU group are not exposed to the Change Club curriculum.

We will disseminate results to the scientific community through peer reviewed publications and presentations and to the communities through presentations and written materials, such as an infographic.

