### Participants

Librarians, with assistance from the research team, will recruit 15–20 participants. Inclusion criteria are age 18 or older, inactive (defined as engaging in physical activity < 3 days per week), ability to walk for at least 20 min, living within the rural community served by the local library, and ability to travel to the local library/location of walking group. Each potential participant will complete the Physical Activity Readiness-Questionnaire (PAR-Q) [50] as part of the screening process to ensure that they are able to participate in walking groups. If the potential participant answers “yes” to any PAR-Q question, they will be asked to obtain healthcare provider authorization to participate. Based on our prior experience in similar populations and settings, we anticipate that this will be non-limiting to recruitment, while ensuring human subject protection. Exclusion criteria include participation/intention to participate in other lifestyle modification program(s), cognitive impairment, inability to communicate due to severe uncorrected hearing loss or speech disorder, and/or severe visual impairment (if precludes completion of assessments and/or intervention).

Recruitment methods will include fliers/postcards/business cards and bookmarks placed at community locations, such as grocery stores, banks, and retail establishments; word of mouth; radio and/or newspaper ads; and press releases sent to local newspapers. Fliers/postcards/business cards or information as worded on the fliers /post cards/business cards may also be posted on the library or city/town government websites and included in printed and electronic versions of library or community organization newsletters.

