Our primary aim will be tested with a linear mixed-effects (multi-level) modeling approach implemented in the lmer package in R. Within this framework, the level-1 and level-2 models will include within-person (e.g., measures across time) and between-person (e.g., intervention assignment) variables, respectively. An additional level will be added to the model to account for nesting within town. Changes in outcomes across time will be modeled as a fixed time effect and model testing will be conducted to determine how best to represent change in each outcome (e.g., linear versus nonlinear). Intervention effects will be examined by specifying fixed-effect dummy variables that compare the intervention groups. Specific hypothesis testing will be by specifying cross-level interactions (time x group contrasts) to determine whether differences across time (e.g., baseline-24 months) significantly vary between intervention groups. Model testing will be used to determine the appropriate random effects structure for each outcome, with the default model including random slopes and intercepts. We will evaluate primary hypothesis tests at traditional significance levels (alpha = 0.05) and use modern methods to control for false discovery rate [77] for post hoc analyses. We will focus interpretation on effect size estimation with accompanying 95% confidence intervals (e.g., Cohen’s d). Model diagnostics (e.g., examining residual/predicted value plots) will be used to confirm statistical assumptions have been met. In the case of violations, more robust alternative models will be employed (e.g., robust mixed-effects models) as appropriate.

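### The rule for choosing random effects does not protect a town-level slope, so the primary time x group test can lose its between-town error term (type I error about 6–10% under assumed clustering of change)

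*Protocol article*

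**What the plan says.** Design and setting: "This study will take place in 20 rural communities in Oregon". Towns are paired on community characteristics, and allocation is by town: "Matched pairs will then be randomized to either a group-based walking program, Step It Up! (SIU) or the combined program (Combined"). Participants: "Librarians, with assistance from the research team, will recruit 15–20 participants", one group per town.

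Data management and analysis describes the primary model. Repeated measures are level 1. Level 2 holds "between-person (e.g., intervention assignment) variables, respectively". Town comes in afterwards: "An additional level will be added to the model to account for nesting within town". The hypothesis test is the time x group contrast at alpha 0.05. On the random effects the plan says: "Model testing will be used to determine the appropriate random effects structure for each outcome, with the default model including random slopes and intercepts". It does not say whether the slopes belong to persons, towns or both, and it exempts no term from removal.

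The limitations paragraph of the Discussion allows that people with large or small change may be concentrated in a few of the 20 groups, because of the leader or the group dynamics. That is town-level variance in change.

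**The concern.** When towns are randomised, the arms differ in mean change partly because towns differ in change for reasons unrelated to the programme. That variation belongs in the standard error of the time x group contrast. A town random intercept satisfies the sentence about nesting, but it shifts every time point in a town equally and so cancels from change. Only a town-by-time term (a town random slope) carries the variation into the test.

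The plan leaves this term to a data-driven choice made outcome by outcome. With 20 towns, a significance test of the town slope often misses a variance that is large enough to matter. When the slope is dropped, the contrast is tested against person-level variation only. The p-values and 95% intervals of the three primary outcomes (physical activity, six-minute walk, collective efficacy) depend on that choice, and the plan centres interpretation on those intervals.

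**Working it through.** **Inputs from the protocol article.** 20 towns, taken as 10 per arm; about 150 participants per arm in the sample size section, so 150/10 = 15 per town; alpha 0.05, taken as two-sided; visits at 0, 6, 12 and 24 months. **Assumed:** ICC of change ρ from 0 to 0.10, because the sample size section mentions a range of ICCs without values; no gain from pairing.

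**The plan's own figures.** Attrition of 10% per year gives 150/0.81 = 186 per arm, inside the planned 175–200. The detectable d of 0.15–0.25 cannot be reproduced exactly, because neither ICCs nor within-person correlations are given. It is attainable without town variance in change: for correlations 0.7, 0.8 and 0.9, a change-score comparison of 150 per arm detects d = 0.251, 0.205 and 0.145. The figure examined below is the nominal 5%.

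**Town slope never fitted.** Scale the total variance of change to 1, with share ρ between towns. The true variance of the arm difference is (2/10) × [ρ + (1−ρ)/15] = (2/150) × (1 + 14ρ). A model without a town slope uses 2/150. Hence

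type I error = 2 × [1 − Φ(1.96/√(1 + 14ρ))].

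Example, ρ = 0.05: 1 + 14 × 0.05 = 1.70; 1.96/√1.70 = 1.503; error 13.3%.

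The ratio was checked in a three-level model with the four visit times. The fitted model had person intercepts and slopes plus a town intercept; the true model also had a town slope. The ratios of true to model-based variance of the time x group coefficient were 1.14, 1.28, 1.70 and 2.40 at ρ = 0.01, 0.02, 0.05 and 0.10, as the formula gives. The town intercept offered no protection.

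**Town slope tested, then kept or dropped.** 400,000 simulated trials per setting, 10 towns per arm, 15 per town, no treatment effect. If kept, the contrast is tested against between-town variation on 18 df (20 towns − 2); if dropped, on person-level df.

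| Assumed ICC of change | Never fitted (formula) | Dropped by 1-df LR test | Overall error, 1-df LR test | Overall error, 2-df LR test | Overall error, AIC (1 parameter) | Always kept, 18 df |
|---|---|---|---|---|---|---|
| 0 | 5.0% | 98% | 4.9% | 5.0% | 4.7% | 5.0% |
| 0.01 | 6.6% | 94% | 6.3% | 6.5% | 5.8% | 5.0% |
| 0.02 | 8.3% | 88% | 7.5% | 8.0% | 6.6% | 5.0% |
| 0.05 | 13.3% | 58% | 8.6% | 10.2% | 6.9% | 5.0% |
| 0.10 | 20.6% | 18% | 6.9% | 8.5% | 5.8% | 5.0% |

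(LR = likelihood ratio; the 2-df test drops the slope variance and its covariance together.)

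With 20 per town, never fitting the slope gives 7.2%, 9.5%, 16.1% and 25.0% at ρ = 0.01, 0.02, 0.05 and 0.10.

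**The case against.** The strongest reply is that the plan is not an intercept-only town model. It adds a town level and names "the default model including random slopes and intercepts", so a town slope may well be in the starting model. That stands. A reader might infer that the plan omits the town slope and analyses the trial as if some 300 individuals had been randomised, with errors of 13–21%. The text does not support this: the term is ambiguous and removable, not excluded. The figures that match the written rule are those averaged over the selection step.

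Four further points also stand.

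- **Detection is not always poor.** At ICC 0.10 the 1-df test keeps the slope in 82% of trials, so it would be wrong to say that such a test hardly ever finds a harmful variance. The weak region is ICC 0.01–0.05, where the slope is dropped in 94% to 58% of trials.
- **The level-2 label is harmless by itself.** Listing assignment among the between-person variables looks like an error, but the fixed-effect column in the mixed model is the same either way.
- **Degrees of freedom are not stated.** A reader might infer that no small-sample method will be used. The article is silent, and an analysis plan that is not shown may settle it. If a normal reference were used with the slope kept, the error would be P(|t₁₈| > 1.96) = 6.6%, but nothing in the text fixes that choice.
- **Matching is ignored above.** If half the town variance in change were shared within pairs (an assumption), the variance ratio on omission would be 15 × ρ × 0.5 + (1 − ρ). That is 1.13 at ρ = 0.02 and 1.325 at ρ = 0.05, giving errors of about 6.5% and 8.9% instead of 8.3% and 13.3%.

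Selecting a random-effects structure from the data is common practice and reasonable for the person-level covariance. It is not a safe way to decide whether the randomised unit contributes to the error term.

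**Conclusion.** The concern holds in a limited form. The rule "Model testing will be used to determine the appropriate random effects structure for each outcome" covers the one term on which the validity of the primary test depends, and nothing in the article exempts it. Under that rule the type I error is about 6–10% for an assumed ICC of change of 0.01–0.10 and 15 completers per town, depending on the ICC and the selection criterion. It reaches about 7–21% only if the slopes in the default turn out to be person-level only, so that the town slope is never fitted. There is no inflation if towns do not differ in change. The ICC values are assumptions, and any benefit of pairing is left out. The protocol's own remark that change may cluster by group makes a zero ICC unsafe to assume. The point should be settled before outcome data are analysed.

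**What to change.** In Data management and analysis, state that:

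1. every primary model contains a town random intercept and a town-by-time (town slope) random effect, whatever model testing shows;
2. model testing is limited to the person-level covariance and the shape of the time trend;
3. the time x group test is based on the number of towns, for example with Satterthwaite or Kenward-Roger degrees of freedom. This supports the first two items and may already be in the analysis plan.

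It would help to describe assignment as a town-level variable, for clarity only.

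The cost is wording, plus slightly wider intervals and slightly less power when town variance in change is near zero. With 18 df the interval multiplier is 2.101 instead of 1.96, so intervals are about 7% wider (2.101/1.96 = 1.07). At ICC 0, the detectable d for a baseline-adjusted comparison with correlation 0.7 and 150 per arm rises from 0.231 to 0.244.

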### Data Collection

Data will be collected at four timepoints (baseline and 6, 12, and 24 months) by trained research staff. Data collection events will be scheduled at each library at each of the timepoints. The SPIRIT flow diagram (Fig. 1) provides the timing of the intervention and assessments for the trial.

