### Sample size calculation

Results of multiple studies have shown that walking group interventions have small to large effects on physical activity. What is unclear is how much advantage can be gained by combining the walking group and civic engagement interventions. To be conservative, we chose to power this study to detect small effect sizes (Cohen’s d ~ 0.20). We calculated the minimum detectable effect (MDE) for the primary cross-level interaction effect testing whether outcome changes across time differs between intervention groups. MDE was estimated using a multi-level framework using Optimal Design software [75] for the planned intention-to-treat (ITT) analyses for the primary outcomes. Multi-level models were used for power analyses using a range of ICCs and all power analyses assumed alpha = 0.05, power = 0.80, continuous normal outcomes, complete cases, two intervention groups, and four time points (baseline-24 months). We estimate that approximately N = 150 participants per intervention group will allow us to detect effect sizes in the small range (Cohen’s d = 0.15-0.25). Given an expected attrition rate of approximately 10% per year, we will recruit 175–200 participants per arm.

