We will examine dropout and patterns of missing data to determine mechanisms (missing completely at random [MCAR], missing at random [MAR], or not ignorable) [78]. In the case of outcome data MCAR or MAR, model-based maximum likelihood estimation underlying the mixed-effects modeling approach (described above) will allow unbiased parameter estimation using all available data (i.e., missing data are handled efficiently with no loss of information). In the case of predictor/covariate data MAR, we will employ principled methods of multiple imputation available in several R packages [79] and Full Information Maximum Likelihood estimation for structural equation modeling. In the case of non-ignorable missingness (missingness related to the outcomes under study), pattern mixture modeling [80] a method for identifying and incorporating patterns of missingness due to non-random drop out, will be used.

Mediation hypotheses (sub-aim 2a) will be tested within a structural equation modeling framework in a series of latent growth longitudinal mediation models [81]. The strength of longitudinal mediation approaches is the ability to use prior time points to predict future time points, thereby eliminating many of the interpretational problems in determining causal direction that occur when testing mediation with cross-sectional data [82]. Similar to the mixed-effects models described above, intercepts and slopes across time will be estimated for all longitudinal variables involved in a proposed mediation (e.g., intervention group → social support → physical activity). This model can then be specified to test causal relationships forward in time. Additional models with different, or even the same, time points at each stage can be fit to determine the strength and timing of any mediation effects. Point and interval estimates (95% CIs) of the mediating (indirect) effects of these paths for each outcome and mediator will be estimated. These models will also take into account higher levels of nesting (e.g., towns) and include important covariates as appropriate.

#### Aim 3

Evaluate program implementation and cost-effectiveness

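### The pattern-mixture analysis depends on a diagnosis of non-ignorable missingness that the observed data cannot give

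*Protocol article*

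**What the plan says.** The rule stands in the protocol article under Data management and analysis and has three steps.

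1. Classify the missingness: "We will examine dropout and patterns of missing data to determine mechanisms (missing completely at random [MCAR], missing at random [MAR], or not ignorable").
2. If it is one of the first two: "In the case of outcome data MCAR or MAR, model-based maximum likelihood estimation underlying the mixed-effects modeling approach" is relied on for unbiased estimates from all available data. The text adds that "missing data are handled efficiently with no loss of information".
3. Otherwise: "In the case of non-ignorable missingness (missingness related to the outcomes under study), pattern mixture modeling" is to be used.

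No other trigger for the third step is given, and nothing says that the pattern-mixture model is fitted regardless, as a sensitivity analysis. Earlier in the same section, the primary aim is assigned to a linear mixed-effects model without any condition on missingness.

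The figures that bear on missing data are under Sample size calculation: "approximately N = 150 participants per intervention group will allow us to detect effect sizes in the small range (Cohen’s d = 0.15-0.25"), and "Given an expected attrition rate of approximately 10% per year, we will recruit 175–200 participants per arm". The power analyses assume complete cases.

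**The concern.** MAR and non-ignorable missingness differ only in whether dropout depends on values that were never recorded, once the recorded values are taken into account. Examining dropout patterns can give evidence against MCAR. It cannot say which of the other two holds, yet that is the distinction on which the rule turns.

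The bracketed gloss in the third step makes this worse. Dropout related to an earlier, recorded outcome is outcome-related in the ordinary sense but can be fully MAR, and the likelihood mixed model then remains valid. Dropout driven by unrecorded later values may leave no decisive trace. The same rule can thus call for pattern-mixture modelling where it is not needed and omit it where it is.

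What is at stake is whether the MAR assumption is tested at all, and whether the decision to test it is taken after the results can be seen. Non-ignorable dropout that differs by arm is plausible here. The Combined program adds a 30-minute session to the weekly 60-minute walk, and people who stop being active may be less willing to attend assessments.

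**Working it through.** **Inputs from the article.** Attrition is about 10% per year and follow-up runs to 24 months. The target is about 150 per arm, with 175–200 recruited. The effect size targeted is d of about 0.20 (range 0.15–0.25). **Assumed, not in the article:** the correlation r between earlier and final values (0.5 and 0.7), and the shift δ of unobserved values from what MAR predicts (0.25 to 0.5 SD).

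**1. The plan's own figure.** Attrition by 24 months is 1 − 0.9² = 0.19 compounded, or 0.20 if added. Inflating 150 gives 150/0.81 = 185.2, so 186, or 150/0.80 = 187.5, so 188. Both lie inside 175–200, so the recruitment range is reproduced. The lower end is tight: 175 × 0.81 = 142 and 175 × 0.80 = 140 would remain at 24 months. The minimum detectable effect cannot be reproduced, because the ICCs and within-person correlations are not given.

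**2. Can the data tell MAR from non-ignorable?** Take 400,000 simulated people with a standard normal baseline and a final value equal to 0.7 × baseline plus residual variance 0.51. Dropout (19.8%) is more likely at low baseline. In data set A the unseen final values follow the same relation as the seen ones (MAR). In data set B they are 0.5 SD lower (non-ignorable).

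| | A (MAR) | B (non-ignorable) |
|---|---|---|
| Observed data | identical to B | identical to A |
| MAR-based estimate of the final mean | −0.001 | −0.001 |
| True final mean | −0.001 | −0.100 |

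No inspection of the recorded values could separate A from B. In both, dropout is related to the recorded baseline outcome, so the article's gloss would fire in A, where the MAR analysis is correct. Now make dropout unrelated to baseline but keep the 0.5 SD shift. The observed data then look MCAR and the gloss stays silent, although the MAR estimate is wrong. More visits do not help, because the shift can always be placed on values after the last one recorded.

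**3. Size of the possible bias.** The bias in the 24-month contrast is (proportion missing × δ) in the Combined arm minus the same product in the SIU arm. With δ = 0 in the SIU arm:

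- 0.19 × 0.25 = 0.048 SD; 0.20 × 0.25 = 0.050 SD
- 0.19 × 0.5 = 0.095 SD; 0.20 × 0.5 = 0.100 SD

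This is about 0.05 to 0.10 SD, or a quarter to a half of d = 0.20. With equal dropout and equal δ in both arms, the two products cancel and the bias is zero.

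**4. The information remark.** Under MCAR loss of a proportion m at the last visit, the variance of the final mean under maximum likelihood, relative to complete data, is r² + (1 − r²)/(1 − m).

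| r | m | Variance ratio | Information kept | SE ratio |
|---|---|---|---|---|
| 0.5 | 0.19 | 1.176 | 85% | 1.08 |
| 0.5 | 0.20 | 1.188 | 84% | 1.09 |
| 0.7 | 0.19 | 1.120 | 89% | 1.06 |
| 0.7 | 0.20 | 1.128 | 89% | 1.06 |

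This is better than using completers alone (80–81%), but some precision is lost. The calculation ignores clustering by town. Losing individuals does not inflate between-town variance, so the loss in the town-level contrast would be smaller.

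**The case against.** The methods named are sound: likelihood under MAR, with a pattern-mixture model for non-ignorable dropout. The article recognises the threat and commits to a method that can address it. The unconditional statement that the primary aim is tested by a mixed model can be read as already fixing the primary analysis, with the MCAR/MAR sentence only saying when that model is unbiased. All of this stands, and it is why the change needed is small.

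Four stronger readings are tempting, and the document does not support them.

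- **That the pattern-mixture analysis would never be run.** The gloss can be acted on: with four visits, one can see whether dropout is related to recorded outcomes. The fault is that this relation does not identify non-ignorable missingness.
- **That it would replace the primary estimate.** The article says only that it will be used, and does not say whether it replaces or supplements the mixed-model result.
- **That the information remark damages the analysis.** In context it explains the use of all available data, and the planners did allow for attrition by raising 150 to 175–200 per arm. It is a matter of wording.
- **That the trial faces a bias of about half its target effect.** This needs the largest assumed shift in one arm and none in the other. It also describes a 24-month difference, whereas the planned test is a time-by-group interaction across visits whose functional form is still open.

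The details of a sensitivity analysis, such as the range of shifts and how results are reported, normally belong in a statistical analysis plan. Their absence here is not part of this point. The trigger rule is stated in the article itself.

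**Conclusion.** The point holds for the trigger. As written, the choice between relying on MAR and modelling departures from it rests on a distinction that observed data cannot make, and on a gloss that draws the line in the wrong place. This follows from the definitions and needs no numerical assumption.

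The consequence is conditional. With 19–20% attrition, a shift of 0.25 to 0.5 SD confined to Combined-arm dropouts would bias the 24-month contrast by about 0.05 to 0.10 SD against a target d of about 0.20. The shifts are assumptions, and the bias could be zero. Missingness on accelerometer-measured activity may exceed attrition, because records without enough valid wear days are also excluded. The article gives no figure for this.

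The information remark is a minor inaccuracy: likelihood estimation uses every recorded value but does not recover the precision lost with missing visits.

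**What to change.** Under Data management and analysis:

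1. State that the likelihood mixed model under MAR is the primary analysis for each primary outcome, whatever the missing-data patterns show.
2. Keep the examination of dropout and missing-data patterns, by arm, as description only, and remove it as the step that selects the analysis.
3. State that a pattern-mixture sensitivity analysis will be run on each primary outcome in all cases. One suitable form shifts unobserved values by a range of deltas, separately by arm. The exact form can be left to the statistical analysis plan, provided it is fixed before outcome data are compared by arm.
4. Drop the gloss that equates non-ignorable with outcome-related missingness, or reword it as dependence on unobserved values given the observed ones.
5. Replace the remark about information with a statement that all observed data are used.

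The cost is a little extra analysis. No new data, visits or participants are needed, and the recruitment target does not change.
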